### Monitoring

#### Collecting, assessing, reporting and managing adverse events

The most common side effects of CRT are myelosuppression, oral mucositis, hand-foot syndrome and peripheral neuritis. More severe side effects are rare. Information about solicited and spontaneously reported AEs will be sought from all participants during telephone reviews by the trial General Practitioner/General Investigator (GP). If a participant reports an AE, the trial GP will determine appropriate action, which may include dose alteration or withdrawal. If an AE is identified as more serious than grade 4, the trial GP will forward this information immediately to the Principal Investigator and Data Safety Monitoring Board. All of the serious AEs (SAEs), suspected adverse reactions and serious suspected unexpected adverse reactions will be recorded immediately in the source documents and on the AE case report form. Each event will be followed until resolution or stabilisation or until it has been determined that the study treatment is not causal. SAEs still ongoing at the end of the study will be followed up to determine final outcome. Any SAE that occurs after the study will be recorded and reported immediately and considered to be possibly related to the study treatment. Economic compensation will be provided by the trial sponsor to those who suffer harm from the trial participation.

For the data monitoring of the QoL outcome, firstly, some measures will be taken to prevent and reduce missing data by enhancing investigator training, communication, patient education and data monitoring. Secondly, we will confirm the causes of missing data case by case and record them in detail. Finally, suitable missing data handling methods such as last observation carried forward (LOCF) or multiple imputation (MI) will be performed.

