Researchers from Hong Kong University initiated an excellent prospective clinical trial to compare the long-term outcomes between DCRT and surgery for ESCC patients. In this study, the overall 5-year survival favours CRT, but the difference did not reach statistical significance (surgery 29.4% and CRT 50%, *p* = 0.147) [13, 14]. The intervention of chemoradiotherapy used in this study is cisplatin 60 mg/m^2^ with hydration therapy given on days 1 and 22, whereas 5-FU is administered as a continuous infusion at 200 mg/m^2^/day from day 1 to day 42. Radiotherapy was delivered as three-dimensional conformal radiation therapy (3DCRT) with a total of 50–60 Gy given in 25–30 fractions over 5–6 weeks. It is inconvenient for patients to be administered 5-FU continuously for 42 days, while IMRT has been reported as more effective and tolerable than 3DCRT. Therefore, we designed this study to investigate the role of DCRT compared with NCRT followed by radical operation in patients with locally advanced ESCC in the highest incidence area worldwide using IMRT (50 Gy/25 F) and different chemotherapy regimens (capecitabine, Xelox, PF, randomised delivery). In the pilot trial, 86 patients finished 16 weeks of follow-up with at least these three regimens in the DCRT group (capecitabine:Xelox:PF = 24:37:25) [19, 20]. The incidences of grade 3–5 AE were 25%, 32.4% and 64% (*p* = 0.03) and the pathological complete response (pCR) rates were 50%, 48.6% and 48% in the three subgroups, respectively (*p* = 0.99). Additionally, objective response rates (ORRs) of 87.5% (21/24), 83.8% (31/37) and 100% (25/25), respectively (*p* = 0.133) were observed. No differences were seen in the complete response (CR) and ORR between the three subgroups. Therefore, it is worth exploring the roles of both the DCRT and single capecitabine in CRT in patients with advanced ESCC using a larger sample size.

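### The trigger for immediate forwarding of adverse events to the Principal Investigator and DSMB, read literally, leaves out grade 4, and no other sentence gives in-study serious events a prompt route to them

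*Protocol article*

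**What the plan says.** The section of the protocol article on collecting, assessing, reporting and managing adverse events sets out four steps.

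- **Detection.** Information on adverse events "will be sought from all participants during telephone reviews by the trial General Practitioner/General Investigator (GP". The trial GP decides what to do when a participant reports an event.
- **Urgent forwarding.** "If an AE is identified as more serious than grade 4, the trial GP will forward this information immediately". The recipients are the Principal Investigator and the DSMB.
- **SAEs during the study.** These, together with suspected reactions, "will be recorded immediately in the source documents and on the AE case report form".
- **SAEs after the study.** "Any SAE that occurs after the study will be recorded and reported immediately". No recipient is named.

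The article names no toxicity grading scale. The only other use of grades is in the Discussion, where the pilot results appear: "The incidences of grade 3–5 AE were 25%, 32.4% and 64" per cent for capecitabine, Xelox and PF respectively.

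**The concern.** A threshold set strictly above grade 4 leaves out grade 4 itself. If the scale ends at 5, the urgent route opens only for grade 5 events. The remaining sentences do not repair this. During the study an SAE is written down promptly, but the text does not say that anyone is told. After the study the text does say that SAEs are reported. The period in which toxicity is most likely thus has the weaker wording.

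What is at stake is how soon the Principal Investigator and the DSMB hear of severe but survivable toxicity. The trial randomises patients 1:1:1 to three chemotherapy regimens within each group, and the pilot showed different toxicity rates across those regimens. A board told at once only of grade 5 events could be late in seeing non-fatal grade 4 events accumulate in one regimen. The efficacy endpoints, the sample size and the analysis are not affected.

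**Working it through.** There is no stated figure to reproduce. The check is a literal reading of the passages against each other, with the pilot counts as context.

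**Step 1: which grades meet the trigger.**
- Condition in the adverse event section: grade strictly greater than 4.
- Highest grade used anywhere in the article: 5 (pilot results in the Discussion).
- Grades that are both above 4 and no higher than 5: {5}. Grade 4 is not included.

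**Step 2: whether another sentence brings grade 4 to the same recipients.**

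| Event | Action stated | Recipient stated |
|---|---|---|
| AE above grade 4 | forwarded immediately | Principal Investigator and DSMB |
| Grade 4 AE, not serious | GP decides on appropriate action | none |
| SAE during the study, including a grade 4 event that is serious | recorded immediately in source documents and case report form | none |
| SAE after the study | recorded and reported immediately | none named |

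Only the first row reaches the Principal Investigator and the DSMB, and only grade 5 falls in it. For in-study SAEs the text stops at recording; for post-study SAEs it goes on to reporting.

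**Step 3: whether the trigger fits its setting.** The forwarding sentence follows telephone reviews in which participants report events. If grade 5 means death, which is the usual convention but is not defined in the article, a participant cannot report the one event that activates the rule. This points to a slip in the wording.

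**Step 4: pilot counts (count = rate × number of patients, "capecitabine:Xelox:PF = 24:37:25").**
- Capecitabine: 0.25 × 24 = 6
- Xelox: 0.324 × 37 = 11.99, so 12 (12/37 = 32.4%)
- PF: 0.64 × 25 = 16
- Total: 6 + 12 + 16 = 34 of 24 + 37 + 25 = 86, or 39.5%

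These counts combine grades 3, 4 and 5. The article gives no breakdown, so the number of grade 4 events that would miss the trigger cannot be derived.

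**The case against.** **The rule may be loosely worded, and it does not forbid other reporting.** Someone may have meant grade 4 and above, and Step 3 makes that plausible. A reader might infer that the trial has chosen to keep grade 4 events from the board. The article does not support that: it sets one mandatory urgent trigger, does not bar other notices, requires SAEs to be recorded at once, and commits to ICH guidelines. The DSMB may also see grade 4 events at routine review. What stands is narrower: the written threshold is wrong or unclear, and staff will follow what is written.

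**An article condenses the full protocol.** The DSMB's review schedule and detailed SAE routing may properly sit elsewhere, and their absence is no finding. This article does, however, state a threshold, recipients and timing. A rule that is stated can be judged as stated.

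**No grading scale is named.** That grade 5 is the top grade, and that it means death, is inferred. This objection is fair. The exclusion of grade 4 does not depend on the inference; the reading of the trigger as fatal-only does.

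**Two stronger readings should not be drawn.**
- A reader might take "More severe side effects are rare" as contradicted by the pilot rates. The sentence follows a list of common toxicities by type and can mean reactions other than those listed. The pilot counts may consist largely of the listed types, and no monitoring rule is derived from the sentence.
- A reader might apply 39.5% to all 196 patients (0.395 × 196 ≈ 77) as the size of the problem. The pilot covered only definitive chemoradiotherapy patients, its regimen mix was 24:37:25 whereas the trial allocates 1:1:1, and the rate includes grade 3 events. It does not measure unforwarded grade 4 events.

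**Sending every SAE at once to the DSMB** would be a choice for the board's charter. The text does not require it, and correcting the threshold does not depend on it.

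**Conclusion.** The point holds as a defect in a stated reporting rule. Read literally, the trigger excludes grade 4, and no other sentence gives in-study grade 4 events or SAEs a stated prompt route to the Principal Investigator or the DSMB. The in-study SAE wording is also weaker than the post-study wording.

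The conclusion rests on the literal meaning of the threshold and on the absence of any other forwarding sentence in the article. That only grade 5 remains, and that grade 5 is fatal, rests on the pilot's use of grades up to 5 and on usual convention.

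The gap concerns immediate forwarding; capture of events is provided for. Its numerical size is unknown. The pilot's 34 of 86 patients with grade 3–5 events shows only that severe toxicity is common enough, in definitive chemoradiotherapy patients, for the trigger to matter. This should be fixed, but it does not threaten the trial's primary comparison.

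**What to change.** Three changes to the adverse event section:

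1. Reword the trigger for immediate forwarding to the Principal Investigator and the DSMB as grade 4 or higher.
2. Name the grading scale and version, so that the threshold has a defined meaning.
3. Reconcile the SAE sentences: state to whom SAEs are reported, and make reporting of in-study SAEs at least as prompt as that of post-study ones.

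The cost is a sentence or two and more notifications for the Principal Investigator and the DSMB to handle. How many more cannot be estimated from the article. Only reporting changes; no dose, withdrawal or treatment rule is touched.

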#### Dissemination

Authorship eligibility guidelines will follow International Committee of Medical Journal Editors (ICMJE) guidelines. The final trial dataset will be available to the investigative team and on reasonable request.

## Discussion

This is the first registered prospective head-to-head clinical trial to compare the outcomes between radical operation and DCRT in patients with ESCC in the highest incidence area worldwide. In the current international guidelines for EC, DCRT is recommended as an effective intervention approach only for patents with local advanced disease but who are not suitable for oesophagectomy. The reasons could be the patient’s willingness, poor performance status, concomitant cardiopulmonary disease and so on. Some studies reported that patients received a survival benefit from DCRT. However, prospective clinical trials that compare DCRT and NCRT plus surgery through a head-to-head method are still limited. Also, the participants who were reported in published studies were mainly western Caucasian patients with oesophageal adenocarcinoma. Sjoquist et al. reported that the EC patients with adenocarcinoma pathology had a higher disease regression rate than those with squamous cell cancer after NCRT [18]. The long-term survival status of patients with ESCC after DCRT or NCRT plus surgery treatment is unclear.

Researchers from Hong Kong University initiated an excellent prospective clinical trial to compare the long-term outcomes between DCRT and surgery for ESCC patients. In this study, the overall 5-year survival favours CRT, but the difference did not reach statistical significance (surgery 29.4% and CRT 50%, *p* = 0.147) [13, 14]. The intervention of chemoradiotherapy used in this study is cisplatin 60 mg/m^2^ with hydration therapy given on days 1 and 22, whereas 5-FU is administered as a continuous infusion at 200 mg/m^2^/day from day 1 to day 42. Radiotherapy was delivered as three-dimensional conformal radiation therapy (3DCRT) with a total of 50–60 Gy given in 25–30 fractions over 5–6 weeks. It is inconvenient for patients to be administered 5-FU continuously for 42 days, while IMRT has been reported as more effective and tolerable than 3DCRT. Therefore, we designed this study to investigate the role of DCRT compared with NCRT followed by radical operation in patients with locally advanced ESCC in the highest incidence area worldwide using IMRT (50 Gy/25 F) and different chemotherapy regimens (capecitabine, Xelox, PF, randomised delivery). In the pilot trial, 86 patients finished 16 weeks of follow-up with at least these three regimens in the DCRT group (capecitabine:Xelox:PF = 24:37:25) [19, 20]. The incidences of grade 3–5 AE were 25%, 32.4% and 64% (*p* = 0.03) and the pathological complete response (pCR) rates were 50%, 48.6% and 48% in the three subgroups, respectively (*p* = 0.99). Additionally, objective response rates (ORRs) of 87.5% (21/24), 83.8% (31/37) and 100% (25/25), respectively (*p* = 0.133) were observed. No differences were seen in the complete response (CR) and ORR between the three subgroups. Therefore, it is worth exploring the roles of both the DCRT and single capecitabine in CRT in patients with advanced ESCC using a larger sample size.

### Trial status

The trial began recruitment in April 2017. Participants will be recruited until December 2020, if necessary.

## Abbreviations

3DCRT: Three-dimensional conformal radiation therapy
5-FU: 5-Fluorouracil
AE: Adverse event
CRT: Concurrent chemoradiotherapy
CT: Computed tomography
DCRT: Definitive CRT
EC: Oesophageal cancer
EORTC: European Organisation for Research and Treatment of Cancer
ESCC: Oesophageal squamous cell carcinoma
EUS: Endoscopic ultrasonography
F: Fraction
IMRT: Intensity-modulated radiation therapy
NCRT: Neoadjuvant CRT
OS: Overall survival
PFS: Progression-free survival
QLQ-C30: Quality of Life Questionnaire-Core 30
QLQ-ES18: Quality of Life-Oesophageal Module 18 Questionnaire
QoL: Quality of life
